## Abstract

**Background:**

Colombia has a long history of an armed conflict that has severely affected communities with forced internal displacement and violence. Victims of violence and armed conflicts have higher rates of mental health disorders, and children and adolescents are particularly affected. However, the mental health needs of this population are often overlooked, especially in low- and middle-Income countries, where scarcity of resources exacerbates the problem that has been further compounded by the global COVID-19 pandemic. Thus, special attention should be paid to the development of interventions that target this population.

**Objective:**

Our research aims to adapt an existing patient-centered digital intervention called DIALOG+ from a clinical setting to an educational setting using stakeholders’ (teachers’ and students’) perspectives. We aim to evaluate the feasibility, acceptability, and estimated effect of implementing this intervention as a tool for the identification and mobilization of personal and social resources to mitigate the impact of social difficulties and to promote mental well-being.

**Methods:**

We will conduct an exploratory mixed methods study in public schools of postconflict areas in Tolima, Colombia. The study consists of 3 phases: adaptation, exploration, and consolidation of the DIALOG+ tool. The adaptation phase will identify possible changes that the intervention requires on the basis of data from focus groups with teachers and students. The exploration phase will be an exploratory cluster randomized trial with teachers and school counselors to assess the acceptability, feasibility, and estimated effect of DIALOG+ for adolescents in school settings. Adolescents’ data about mental health symptoms and wellness will be collected before and after DIALOG+ implementation. During this phase, teachers or counselors who were part of the intervention group will share their opinions through the think-aloud method. Lastly, the consolidation phase will consist of 2 focus groups with teachers and students to discuss their experiences and to understand acceptability.

**Results:**

Study recruitment was completed in March 2022, and follow-up is anticipated to last through November 2022.

**Conclusions:**

This exploratory study will evaluate the acceptability, feasibility, and estimated effect of DIALOG+ for adolescents in postconflict school settings in Colombia. The use of this technology-supported tool aims to support interactions between teachers or counselors and students and to provide an effective student-centered communication guide. This is an innovative approach in both the school and the postconflict contexts that could help improve the mental health and wellness of adolescents in vulnerable zones in Colombia. Subsequent studies will be needed to evaluate the effectiveness of DIALOG+ in an educational context as a viable option to reduce the gap and inequities of mental health care access.

**Trial Registration:**

ISRCTN Registry ISRCTN14396374; https://www.isrctn.com/ISRCTN14396374?q=ISRCTN14396374

**International Registered Report Identifier (IRRID):**

DERR1-10.2196/40286

## Introduction

Colombia has traditionally been considered a violent country as a consequence of a long internal armed conflict, which has caused high rates of internal displacement and violence [1]. The number of individuals affected by this conflict has been estimated to approach 9.2 million [2], and despite the peace agreements signed in 2016, the problem persists in many regions of the country [3]. Worryingly, it is estimated that approximately 700,000 people have been affected by internal displacement ever since these agreements were reached [4].

One of the most affected regions in Colombia is the department of Tolima. Its central-western location in the country has made it a strategic corridor for trafficking of narcotics and the armed conflict [5]. Within Tolima, certain rural municipalities including Chaparral, Rioblanco, and Planadas have been particularly affected because of the connection they provide between the Pacific region of Colombia and the center of the country [6]. To prioritize these municipalities, which have been constantly subjected to armed conflict, in 2017, the Colombian government designated territories including Chaparral and Rioblanco as part of a Development Program with a Territorial Approach (PDET). This program aims to accelerate transformation and access to services for the people living in these regions [6,7].

The impact of armed conflict on the people inhabiting these regions is considerable, and international crises and wars have unveiled the consequences that these conditions have on mental health. Several studies demonstrate that individuals displaced by violence are at an increased risk of mental health disorders [3,8,9]. These include posttraumatic stress disorder (PTSD), depression, anxiety, and mood and sleep disorders, among others [10,11]. Even more concerning is the impact that these conflicts have on children and adolescents—a population that tends to have higher susceptibility to mental health conditions [12]. This may be due to the key psychological, biological, and social changes that characterize this period of life [13].

In Colombia, the National Mental Health Survey conducted in 2015, using screening scales, calculated a lifetime prevalence of any mental health disorder of 4.7% in children aged between 7 and 11 years and of 7.2% in adolescents aged 12 to 17 years [14]. Additionally, and in accordance with the worldwide trend, mental health conditions seem to be more prevalent in children and adolescents who have been subjected to internal displacement: the prevalence of an anxiety disorder and PTSD was higher (6.5% and 13.2%, respectively) in children (aged 7 to 11 years) who had experienced displacement due to violence, compared to an estimated prevalence of 1.8% for any anxiety disorder and 6.6% for PTSD in those who had not gone through the same experience [15]. Similarly, the 12- to 17-year-old group who had been displaced had a higher prevalence of any anxiety and depression disorders. Worryingly, the same significant difference in prevalence was reported for suicidal thoughts (19.8%) and suicide attempts (9.1%), which were higher in those who were displaced than in those who were unaffected (5.8% and 2.1%, respectively) [16].

Despite this clear problem and multiple issues, both governmental and individual barriers persist and impede an adequate response to the mental health needs of this vulnerable population [17]. It is estimated that in low- and middle-income countries, there is a significant shortage of mental health professionals such as child psychiatrists, accounting for only 0.1 per 100.000 population [18]. In Colombia, there are 1584 psychiatrists, which implies that there are 3 psychiatrists for every 100,000 inhabitants. However, psychiatrists are concentrated in the capital cities, which prevents access to people in rural areas owing to travel, time, and costs. This is an especially significant barrier to children and adolescents' access to mental health services [19]. Furthermore, the treatment gap (the gap between those requiring and receiving adequate treatment) for mental health disorders in children and adolescents of Central and South America has been estimated to be between 64% and 86%, which is an alarmingly high estimate [17]. According to the Pan American Health Organization, the treatment gap for any mental health disorder in Colombia is 86.1% and was the highest of all the countries in the Americas, followed by Guatemala (84.9%) and México (81.4%) and including the United States (58.9%) [20]. Moreover, the recent COVID-19 pandemic and its restrictions have exacerbated mental distress. Many studies have identified particular stressors that the COVID-19 isolation measures had on children and adolescents: lack of social contact, lack of personal space at home, separation from parents or caregivers, and concerns about academic and social impacts [21,22], all of which can lead to the development of anxiety or depressive disorders [23-25]. As in most countries, lockdown measures have been eased as of this writing, and it is important to keep investigating the impact that these restrictive measures had on children and to consider that the results obtained have to be viewed in a postquarantine context.

The aforementioned barriers, as well as the scarcity of funds allocated to mental health and the lack of education about and community knowledge of mental health issues, can perpetuate the stigma and false beliefs that surround mental health disorders. The lack of education and community knowledge highlights the essential role that teachers and school counselors can play in promoting mental health, well-being, and resilience in children and adolescents [26]. One of the biggest challenges in Colombia relates to the lack of personnel trained in mental health in schools in rural areas where there is usually only 1 counselor per school, who is not always a psychological professional. Interventions that aim to increase and inculcate skills concerning mental health in educators (such as courses or capacity development initiatives that focus on mental health) are fundamental [26,27].

Likewise, the school environment allows a constant interaction among teachers, counselors, and their students, which encourages the creation of a bond based on trust and provides the educators a chance to identify potential mental health disorders [28]. Therefore, an approach to mental health issues in the school setting can aid in overcoming some of the previously mentioned barriers [29].

To promote this approach in schools, we propose implementing an existing patient-centered digital intervention called DIALOG+, which was developed to facilitate the interaction between the clinician and patients with mental health issues [30-33]. This has primarily been implemented in mental health care settings. However, its adaptation outside of the clinical context and into the school context is innovative and has not been attempted before. Through this study, we aim to evaluate the feasibility of implementing DIALOG+ in the educational setting through teachers and counselors as a tool for the identification and mobilization of personal and social resources to mitigate the impact of social difficulties and to enhance quality of life.

## Methods

### DIALOG+

This tool is a resource-oriented, evidence-based intervention developed to facilitate the interaction between the clinician and patients with a mental health condition, allowing patients to actively participate in clinical meetings [34]. By structuring the interaction that takes place during routine clinical meetings, it encourages self-reflection and expression and empowers patients to improve their mental and social situation themselves. The intervention is supported by an app that can be installed on multiple electronic devices (eg, a tablet or cellphone).

During consultation, and with a patient-centered assessment, DIALOG+ invites the individual to evaluate their satisfaction with 8 life domains (mental health, physical health, work, accommodation, leisure activities, friends, relationship with family or partners, and personal safety) and 3 treatment domains (medication, practical help, and professional appointments). Each item is rated on a scale of 1=“totally dissatisfied” to 7=“totally satisfied,” and patients are asked if they would like additional help with that domain.

Scores are summarized and displayed on the app at subsequent meetings, allowing comparisons with previous scores from previous meetings. Physicians provide positive feedback on any domain showing improvement. This is followed by a 4-step, solution-focused approach to identify psychosocial resources to intervene in up to 3 domains, which the patient has identified as needing assistance to improve their quality of life. DIALOG+ is an evidence-based and effective intervention [32] that has shown to save up to £1345 (US $1510.80) per patient for the UK health system, mainly owing to fewer days of hospitalization among individuals receiving the intervention [30,35].

### Intervention and Study Design

#### Overview

This study will adapt the DIALOG+ intervention through a mixed methods study. The quantitative component comprises an exploratory cluster randomized controlled trial. Initially, we will measure variables concerning mental health, resilience, quality of life, and social, and familiar functionality. These will be measured once more after the intervention stage. The qualitative component consists of conducting focus groups with teachers and students, and the think-aloud method [36] to obtain insights into the DIALOG+ adaptation in the school setting.

The study design has 3 phases: adaptation, exploration, and consolidation (Figure 1).

**Figure 1 figure1:**
[figure not shown]
Adaptation, exploration, and consolidation phases.

#### Adaptation

We will present the existing DIALOG+ tool to teachers and adolescents between 12 and 18 years of age during focus groups to obtain end users’ insights into adaptation strategies of DIALOG+ for the Colombian educative context. We will conduct one focus group with adolescents and another one with teachers and educators recruited through convenience sampling. Each focus group will include between 5 and 8 participants who will first sign an informed consent or assent form, and they will then be audio recorded for transcription and analysis. The information obtained in this phase will be key for adapting the intervention and for developing the following phase of the study.

#### Exploration

This phase consists of an exploratory cluster randomized trial with 14 teachers and school counselors in Chaparral, Tolima. This specific phase will assess the acceptability, feasibility, and estimated effect of applying the DIALOG+ intervention in school settings. Teachers and their students (who together form a cluster) will be randomly allocated to either the experimental (DIALOG+) group or an active control group (counseling as usual). Teachers will act as the unit of randomization with clustering by teacher to prevent contamination effects within the study. Accordingly, we will have 14 clusters comprising 1 teacher and 5 students each. The unit for randomization will be teachers in a ratio of 10:4 to the intervention and the control groups to maximize our data on feasibility and acceptability of the intervention, while providing some comparison data in the control group to estimate effect. Teachers will be recruited first, and they will then identify eligible students. Each teacher will invite 5 adolescents who they consider to be in need of counseling or additional support for presenting a personal, family, or social situation that is affecting their performance at school or their well-being. Students who accept the invitation will be asked to sign the assent and informed consent of their parents. Participants will be excluded from the study if they intend to change towns or school in the near future, or if they cannot participate for the full duration of the study. The teachers will determine the students with whom they will participate in the study. Teachers and their students (who together form a cluster), will be randomly allocated to either the experimental (DIALOG+) group or to an active control group (counseling as usual) by the study coordinator who is blinded to their identities. Each teacher or counselor will be in charge of 5 students during the intervention for a total of 70 students (Figure 2).

Prior to randomization, the selected adolescents will complete a self-administered baseline questionnaire to collect their sociodemographic data and measure symptoms of different mental health disorders.

The following 8 instruments will be used: the Family adaptability, partnership, growth, affection, and resolve; the Self-Reporting Questionnaire to assess mental health problems; the 8-item Patient Health Questionnaire depression scale, to assess depression symptoms; the Generalized Anxiety Disorder 7-item scale to assess anxiety symptoms; the PTSD Checklist to measure symptoms; the 25-item Connor Davidson Resilience Scale to measure resilience; the Rosenberg scale to measure self-esteem; and the Manchester Short Assessment of Quality of Life to measure quality of life.

These will be administered by research assistants who are blinded to the arm allocation and will be repeated at the end of the follow-up.

The experimental intervention will be carried out using DIALOG+, for which each teacher will be provided a tablet with the application and will undertake a 90-minute standardized training session on its use. DIALOG+ consists of 2 main parts: (1) a person-centered assessment, whereby the teachers invite the students to rate their satisfaction with different life domains, followed by (2) a 4-step approach based on the principles of solution-focused therapy [34]. Following review of the scores across the DIALOG scale, which includes comparing the current ratings with the ratings obtained from any previous session, up to 3 of the areas that are listed on the DIALOG scale are chosen to be discussed in more detail. The 4-step solution-focused approach is used to structure the discussion to identify patients’ resources and develop solutions to deal with the adolescents’ concerns. At all times, the ratings on the scale are referred to in order to underpin and contextualize the discussion. Step 1, *Understanding*, elicits contextual information about the area under discussion and establishes what is working in that area. Step 2, *Looking Forward*, asks the adolescent to adopt a future perspective and think about the “best-case scenario” within that domain as well as the smallest improvement that can be made to incrementally move up the rating scale. Step 3, *Considering Options*, invites the adolescent to reflect on what he/she and others can do to improve their quality of life. Finally, step 4, *Agreeing on Actions*, summarizes the discussion, and a list of actions is generated and input into the application. Ultimately, the teacher and student together will develop an action plan comprising individual action items for each of the discussed areas to be completed before the next session.

The control arm’s meetings will be conducted in the usual manner as teachers conduct counseling. Considering that most teachers have no training in the use of psychological techniques, it is not expected that they will be used.

During this phase, teachers who were assigned to the intervention group will record voice notes expressing their thoughts and opinions about the implementation process using the think-aloud method.

We will assess process measures to better understand the feasibility of the intervention for application in schools in Colombia. We will assess teacher and student recruitment and retention when reporting reasons for refusal and reasons for loss to follow-up, as well as the number and frequency of sessions conducted in both arms. Feasibility criteria will include recruitment of at least 85% of anticipated participants and a retention rate of at least 75%. We will also have at least two-thirds of sessions completed as planned (on average at least 4 sessions) as an additional feasibility criterion.

**Figure 2 figure2:**
[figure not shown]
Exploratory cluster randomized trial.

#### Consolidation

Finally, we will conduct 2 focus groups with teachers and students. Both groups will be asked to discuss their experience, perceptions, and possible changes or modifications required to adapt DIALOG+ to the school setting. Adolescents will be asked if they perceived changes in their mental well-being. The data obtained will help assess the viability of using DIALOG+ in a school context in vulnerable populations in postconflict areas in Colombia.

### Participants

This study will take place in one PDET the Chaparral municipality of Tolima. The recruitment of school teachers or counselors and adolescents will take place in 2 public schools through invitation. Each teacher will invite 5 adolescents whom they consider to be in need of counseling or additional support. Participants will be excluded from the study if they intend to change towns or schools in the near future or if they cannot participate for the full duration of the study.

All adolescents and their parents or guardians and teachers will be asked to provide assent and informed consent by signing an assent and informed consent form before any data collection begins. During the consent process, researchers will ensure that participants and parents or guardians are aware of their right to decline participation at any stage of the study and that withdrawing participation will not affect their rights or access to support.

Participants who withdraw from the study will be able to ask for their data to be removed from analysis. If a participant wishes to withdraw from the study, researchers will record the date of withdrawal and reasons for withdrawal (if provided).

### Sample Size

Consistent with the exploratory study design, convenience sampling will be performed. We will conduct the study with 14 teachers and 70 students. The population of adolescents attending the 2 participating schools is 1494. However, the number of participating teachers is limited both by the number of teachers in each school and by the capacity of the teachers to conduct counseling. In each school, there is only one school counselor who is a psychology professional. The teachers who conduct counseling do so because they are interested in the well-being of their students. This is an exploratory study to determine whether it is feasible and acceptable to adapt DIALOG+ in the school setting, with quantitative outcomes to provide estimates of effects that could be used to design a larger study if our findings are supportive of this. Since this is an exploratory trial, the power to detect meaningful differences with statistical significance will be limited. With an intraclass correlation coefficient of 0.05, which we estimated from other studies we have conducted, the planned sample size will allow us to detect an effect size of 0.80 with 78% power and a smaller effect size of 0.5 with 40% power. In the case of the Manchester Short Assessment of Quality of Life, usually the primary outcome in DIALOG+ studies, an effect size of 0.80, would be equivalent to a change of approximately 6 points in total (eg, 1 point on a 7-point scale each on 6 out of 12 items, or 3 points each on 2 areas of life), which reflects a meaningful change.

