### Data Management and Analysis

This study will use a mixed methods design. Quantitative and qualitative aspects will be triangulated in the overall evaluation of the intervention. Both qualitative and quantitative results will be presented for a global analysis of the intervention. For variables measured at 2 time points (baseline and 6-month follow-up), we will report measures of central tendency and dispersion in accordance with the data distribution, and significance tests will be performed. The analysis will use intention-to-treat analysis by including all students in the arm to which they were randomized, whether or not they received the intervention, and including all students in the analysis by using multiple imputation where outcomes are missing. To generate parameter estimates for any changes in outcomes for students using DIALOG+, mean differences (with standard deviations) and effect sizes over 2 time points (baseline and after the intervention period) will be calculated.

Qualitative data will be analyzed using thematic content analysis techniques [37]. Qualitative data will be analyzed using a framework of theoretical domains of behavioral change to understand the experience and issues concerning behavioral change that could be related to the acceptability and use of DIALOG+, as well as possibilities for improving implementation. This will serve to develop concrete plans for the implementation and evaluation of the strategy, such as clinical trials that evaluate the effectiveness of the tool with a larger number of participants. All interviews will be transcribed and analyzed using NVivo software [38], which creates graphical displays and facilitates thematic content analysis.

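### The stated power of 78% and 40% uses a student-level or normal reference distribution; with 14 randomised teachers (12 df) the same inputs give about 72% and 36%

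*Protocol article*

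**What the plan says.** The Exploration section makes the teacher the unit of randomisation: "The unit for randomization will be teachers in a ratio of 10:4 to the intervention and the control groups", and "we will have 14 clusters comprising 1 teacher and 5 students each". The Sample Size section repeats the totals ("We will conduct the study with 14 teachers and 70 students"), gives the correlation ("With an intraclass correlation coefficient of 0.05, which we estimated from other studies we have conducted") and states that the sample can "detect an effect size of 0.80 with 78% power and a smaller effect size of 0.5 with 40% power". It equates an effect of 0.80 with about 6 points in total on the Manchester Short Assessment of Quality of Life. It gives no alpha, sidedness, degrees of freedom or allowance for loss to follow-up.

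The feasibility criteria in the Exploration section include "a retention rate of at least 75" per cent. Data Management and Analysis plans significance tests and an intention-to-treat analysis, "including all students in the analysis by using multiple imputation where outcomes are missing". It names no model or test for comparing the arms. The Sample Size section and the Discussion both say that power is limited, and the Discussion calls feasibility and acceptability the primary aim.

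**The concern.** A design effect corrects the variance of the difference between arms for clustering. It does not correct for the fact that this variance must be estimated from few clusters, here 14, of which only 4 are controls. The reference distribution for a contrast between randomised teachers should therefore reflect the number of teachers, not the number of students. If the power was calculated as though 70 students supplied the degrees of freedom, it is too high for the design described.

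These two percentages are the only numerical operating characteristics given for the effect comparison, and the estimates are meant to inform a larger trial. A reader interpreting a null or positive result, or planning that trial, would start from a figure that is somewhat too favourable.

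**Working it through.** **Inputs.** From the Exploration section: 10 and 4 clusters of 5, so 50 and 20 students. From Sample Size: ICC 0.05 and effect sizes 0.80 and 0.50 SD. Assumed, because not stated: two-sided alpha 0.05. One-sided testing does not reproduce the stated figures (86.8% and 53.2% with a normal reference).

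**Step 1: reproduce the stated power.**
- Design effect = 1 + (5 − 1) × 0.05 = 1.20.
- SE of the difference, in SD units = √[1.20 × (1/50 + 1/20)] = 0.2898.
- Noncentrality = 0.80/0.2898 = 2.760, and 0.50/0.2898 = 1.725.

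| Reference distribution | Power at 0.80 | Power at 0.50 |
|---|---|---|
| Normal | 78.8% | 40.7% |
| t, 68 df (70 students − 2) | 77.7% | 39.8% |
| Stated in the article | 78% | 40% |

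The 68-df row rounds to both stated figures. Clustering and the 10:4 split are therefore included. The small number of clusters and any attrition are not. Omitting the design effect (85.6%, 47.2%) or using equal allocation (86.3%, 48.0%), both with a normal reference, does not fit.

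**Step 2: cluster-level degrees of freedom.** With df = 14 − 2 = 12, the two-sided 5% critical value is 2.179, against 1.995 on 68 df. The noncentrality is unchanged. Noncentral t gives **71.7%** at 0.80 and **35.5%** at 0.50. A simulation of cluster-mean t tests (200,000 runs) gives 71.7% and 35.5%, with type I error of 5.0%.

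**Step 3: detectable effect.** On 12 df, 78% power needs a noncentrality of about 2.98, so the effect is 2.98 × 0.2898 = 0.86 SD. On the article's scale (0.80 SD is about 6 points) that is 0.86/0.80 × 6 = about 6.5 points.

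**Step 4: sensitivity to retention at the 75% floor.** Loss is assumed to be spread evenly over clusters.
- Students per cluster = 5 × 0.75 = 3.75, so 37.5 and 15 students.
- Design effect = 1 + 2.75 × 0.05 = 1.1375.
- SE = √[1.1375 × (1/37.5 + 1/15)] = 0.3258.
- Noncentrality = 2.455 and 1.535; power on 12 df is about 62% and 29%.

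Simulation with random 75% retention gives 60.8% and 28.9%.

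**Step 5: sensitivity to baseline adjustment.** The variance is multiplied by 1 − r². For an assumed baseline correlation r of 0.3 to 0.5, power on 12 df is 76–83% (0.80) and 38–45% (0.50) with full follow-up, and 66–74% and 32–37% at 75% retention.

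**The case against.** **The arithmetic is sound on its own inputs.** This stands. The authors dealt with the two larger issues, clustering and unequal allocation. What is at issue is the choice of reference distribution, which costs about 4 to 6 percentage points.

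**Power depends on the analysis, which the article does not specify.** This stands in part. Outcomes are measured at baseline and follow-up, and an adjusted analysis could reach or exceed 78% and 40% on 12 df. But the calculation that reproduces the stated figures contains no adjustment and the article claims none, so an unstated adjustment cannot support them.

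**A reader might infer that the true power is 62% and 29%.** The documents do not support that. The 75% is the minimum for calling the study feasible, not an expected rate, and the Sample Size statement concerns the planned 70 students. Students who expect to move, or who cannot take part throughout, are also excluded. The lower figures are a sensitivity case. Multiple imputation does not remove the need for it, since imputing outcomes does not in general restore the lost information.

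**The limitation is already disclosed.** This stands as to weight. A general caveat does not make a specific percentage correct, but it lowers the risk that anyone is misled. The sample was set by convenience and teacher capacity, not by this calculation.

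**Conclusion.** The stated 78% and 40% are somewhat optimistic for a trial that randomises 14 teachers. At the article's own ICC of 0.05, with two-sided alpha 0.05 (assumed), complete follow-up and an unadjusted comparison on 12 df, power is about 72% and 36%. The effect detectable with 78% power is about 0.86 SD rather than 0.80.

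Severity is minor to moderate. The feasibility criteria do not depend on power, and the comparison is exploratory. It would be wrong to conclude that the trial is invalid or must be enlarged: the article claims neither adequate power nor a confirmatory purpose.

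**What to change.** In Sample Size, replace the power sentence with text to this effect: *With 10 and 4 clusters of 5, ICC 0.05, two-sided alpha 0.05, complete follow-up and no baseline adjustment, power allowing for 12 cluster-level degrees of freedom is about 72% for an effect size of 0.80 and 36% for 0.50.* The authors should confirm the alpha, which is assumed here.

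Add as a labelled sensitivity: *At the 75% retention floor of the feasibility criteria, power would be about 62% and 29%.*

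Optionally, report the expected precision. The half-width of the 95% confidence interval is 2.179 × 0.2898 = about 0.63 SD with full retention, and 2.179 × 0.3258 = about 0.71 SD at 75%.

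The cost is a change of text and less favourable figures. Sample size, conduct and participants are unaffected.
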